#### Planned subgroups

Where applicable, subgroups will be:

Patients in whom an E-SN toolkit entry was completed.Patients diagnosed with cancer.

#### Data display and reporting

We will combine or suppress any cells with small numbers (under 5) of observations to prevent any potential identification during the reporting of the results.

### Patient and public involvement

We have recruited an experienced patient and public involvement (PPI) representative to sit on the project steering committee. She has been involved in planning how PPI involvement will best fit in with the project, and will attend steering committee meetings to discuss project progress, as well as cochairing workshops with patient representatives. We anticipate involving five additional patient representatives. The PPI collaborators will be involved in interpreting the findings of the study and identifying which of the prespecified outcomes are of greatest importance to patients. This will allow them to consider whether there would be a beneficial effect in terms of patient perspectives, even if the E-SN toolkit caused only a small change in outcomes.

## Ethics and dissemination

### Informed consent

Practices that are randomised to take part in the study will be provided with a welcome pack by their RCGP RSC PLO team. The pack includes a practice information leaflet (online supplementary appendix B) and practice poster (online supplementary appendix C), a copy of the protocol, and a copy of the ethical approval documentation, providing the practice with detailed information about the exact nature of the study; study requirements; the implications and constraints of the protocol; and any risks involved in taking part. Site agreements will be in place with each practice and it will be clearly stated that the practice is free to withdraw from the study at any time for any reason, without affecting their legal rights, and with no obligation to give the reason for withdrawal. Signing a site agreement will form consent for a practice to take part in the study.

10.1136/bmjopen-2020-038562.supp2Supplementary data

10.1136/bmjopen-2020-038562.supp3Supplementary data

No direct or active involvement will be required from consulting patients and we will not be seeking individual patient consent. The rationale for obtaining agreement at the cluster (practice) level is that the activation of the Toolkit will be through the EMIS Web software system and healthcare practitioners are the intended recipient of the intervention.^37 38^

Patients who have opted out of sharing data are not processed by the RCGP RSC and therefore will not be accessed the research team and their data will not be extracted. RCGP RSC does keep a count of opt-out patients per practice as this is needed to interpret rates collected for surveillance, this runs at around 2% of the registered population.

A patient notification in the form of a poster will be displayed in all participating practices giving patients information about the study and how to opt out of data sharing. Outcome data will be extracted from coded data in the EHR by the SQL developer and provided in a pseudonymised form to the analysis team.

### Safety reporting

As patients remain under their GP’s care throughout the study, and serious adverse events such as death and hospitalisation unrelated to the study are expected in this patient group, no formal monitoring of serious adverse events will be carried out.

### Quality assurance

The study may be monitored, or audited in accordance with the current approved protocol, Good Clinical Practice (GCP), relevant regulations and standard operating procedures by responsible individuals from the sponsor and the NHS trusts in which it is being carried out.

### Ethical and regulatory considerations

Ethical approval has been obtained from the North West—Greater Manchester West NHS Research Ethics Committee (REC Reference 19/NW/0692). We have also obtained Health Research Authority (HRA) approval to carry out the study in the NHS. The study sponsor is the University of Oxford, UK ([contact]). All substantial amendments to the protocol will be submitted to the sponsor, the ethics committee, and the HRA, and, where necessary, their approval will be obtained.

The investigator will ensure that this study is conducted in accordance with relevant regulations and with GCP. The university has a specialist insurance policy in place which would operate in the event of any participant suffering harm as a result of their involvement in the research (Newline Underwriting Management, at Lloyd’s of London). NHS indemnity operates in respect of the clinical treatment that is provided. All participants will continue to receive NHS care during and after the study.

### Patient confidentiality

The study staff will ensure that the practices’ patients’ anonymity is maintained. The practice patients will be identified only by an ID number on all study documents and any electronic database.

All documents will be stored securely and only accessible by study staff and authorised personnel. The study will comply with the UK General Data Protection Regulation and Data Protection Act 2018, which require data to be anonymised as soon as it is practical to do so. Pseudonymisation will be carried out using the RCGP RSC standard processes and will ensure that it is not possible for research staff to link study data with data from other sources. Although multiple items will be extracted from individual clinical records, we have taken care to minimise the number of data items/variables made available for this analysis, for example, using age rather than date of birth. RCGP RSC apply a process of statistical disclosure control to ensure that individuals cannot be identified, even from aggregate data. For example, data might have to be exported by 5-year or 10-year age bands if there were small numbers in an individual year of birth.

Data are held on a protected by a firewall secure server at the University of Surrey, currently acting as the RCGP RSC’s data and analysis hub. All in-bounded connections are blocked, but out-bounded connections are allowed on approval by a senior staff member.

The secure server is managed by the Clinical Informatics and Health Outcomes Research Group, and will be moved to the University of Oxford where the Group is based. It meets the requirements of NHS Digital’s Data Security and Privacy toolkit.

### Dissemination

The primary results of the study will be published in a peer-reviewed journal publication. Additional dissemination may take place via peer-reviewed conference presentations, and additional journal publications. Participating general practices will receive a report of the main findings, and results will also be disseminated on both the University of Oxford Nuffield Department of Primary Care and RCGP RSC websites. Patients will not be directly informed of the results, but will be able to access results on the internet if they so wish.

Authorship of all publications will be determined in accordance with the International Committee of Medical Journal Editors guidelines.

The final trial dataset will consist of a large quantity of pseudonymised participant-level data extracted from clinical records. Due to the potentially sensitive nature of this data, and to ensure compliance with relevant data protection law, this data will only be made accessible to the subgroup within the research team who will be carrying out the analysis, and there are no plans for granting public access to the data.

The full protocol will be made available as part of the study ISRCTN registration details following publication of this paper. Statistical code will be available from the authors on request.

### Cancer diagnosis in the time of COVID-19

The COVID-19 pandemic has led to considerable changes in general practice, including a switch from predominantly face-to-face consultations to remote consultations by telephone or video call. In addition, many non-urgent hospital outpatient consultations and investigations have been cancelled or delayed, and it is likely that patients are less willing to consult with clinicians for what they perceive as ‘minor’ conditions, due to a desire to reduce pressure on the health service. All of these factors are likely to impact on cancer diagnosis and referral.

As a result, the initiation of the CASNET2 study has been delayed in an attempt to minimise the effect of these factors on the results of the study, and to ensure that the results are generalisable. However, we also intend to carry out supplementary downloads from participating practices for the 12 months prior to March 2020 (baseline comparison period) and for the entire pandemic period, or until 31 October 2020, whichever is latest.

We will then conduct a before-and-after analysis of the following outcomes:

Presenting symptoms of cancer.Primary care interval for cancer diagnosis.Proportion of cancers detected after emergency presentation.Site and stage of new cancersTotal time to diagnosis.Number of consultations in primary care interval.Rates of patients completing direct access cancer investigations.Rates of patients referred by 2-week wait, urgent and routine routes.

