## Methods and analyses

### Outcomes and outcome definitions

#### Primary outcome: primary care interval for cancer diagnoses

The primary care interval is defined as the number of days between the first recorded symptoms of cancer (within the year prior to diagnosis) and subsequent referral for secondary cancer care.^22^ In line with published research and guidelines on diagnostic intervals, we will search the patient record for coded symptoms during the year prior to diagnosis for all patients with a cancer diagnosis: 1 year is a trade-off between misattributing unrelated symptoms occurring more than a year before and missing symptoms of relevance by restricting to a shorter period.^22 23^

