### Data extraction

Data extractions from all participating practices will correspond to two major time points: at the start of the introduction to the stepped wedge implementation of the E-SN toolkit, and at the end of the stepped wedge period (12 months later). At these two time points, consultation data from the participating practices will be obtained for the previous 24 months. Data from the previous 24 months are required to identify cancers detected in 12 months prior to start, plus the first recorded symptom of cancer during the primary care interval, allowing for this interval to cover up to a year prior to diagnosis.

Records from all patients who are adults aged 18 years and above, registered at participating practices and who have not opted out of sharing data for research purposes will be extracted. Pseudonymised patient information will include: demographic information of age, sex, dates of clinical consultations; coded consultation data for symptoms, diagnoses, tests ordered and referrals made within the consultation records. Where a definitive diagnosis has been made (for cancer and non-cancer conditions), the clinical features recorded in the year prior to diagnosis will be captured. These actions will be achieved by extraction of the EHR rather than by hand searching notes.

Practices will be asked to search for open diary entries every week during the intervention period, and to download and save these to an Excel spreadsheet (locally). The central study research team will use these spreadsheets to track which diary entries are closed during the course of the intervention.

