### Statistical analysis

In patients with a diagnosis of cancer, we will calculate the primary outcome of primary care interval (time between first recorded symptom and referral), proportion diagnosed after emergency presentation and the recorded diagnosis. Among consulting patients, we will calculate the rate of direct access cancer investigation and rates of referrals via 2 weeks wait, urgent and routine pathways, as well as the number of consultations during the primary care interval, and the template activation rate. A patient referred to: a 2-week wait pathway will be reviewed by a specialist within 2 weeks; an urgent pathway will be reviewed as a priority but the exact timing varies between specialty and healthcare setting; a routine pathway requires specialist review but on a non-urgent basis.

Regarding the analysis of the stepped-wedge design and the effect of correlation of observations within clusters, will model the association using a fixed effect for the intervention condition of the cluster at each time step, a fixed effect for time and other covariates (eg, changes in cancer guidelines), and then include a random effect for practice and a random effect for patient to account for correlation of the observations from the same centre and from the same participant.

Analyses will include all patients registered at participating practices. Practices that withdraw their agreement to participate will be included in analyses up to the point of withdrawal, unless they indicate that they wish to withdraw previously collected data from analysis.

Our primary analysis will be carried out on an intention to treat principle. Therefore, if any practice does not switch on the E-SN toolkit at the correct time for their cluster, we will carry out the analysis under the assumption that the E-SN toolkit was switched on at the correct time.

The primary care interval is defined from the presence of symptoms and referral in the primary care record. Symptoms of interest will include all symptoms included in the urgent referral guidelines including vague symptoms such as weight loss, tiredness and back pain.^35 36^ Missing data for these variables in the record will be interpreted as the absence of symptoms or referral, respectively. Extracted data from the primary care record will be limited to the study period plus the preceding year, so symptoms recorded prior to this will not be visible to the research team.

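### Read literally, the COVID baseline download omits the look-back year, truncating first symptoms for baseline cancers but not for pandemic cancers; the pandemic window also has no cap at toolkit activation

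*Protocol article*

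**What the plan says.** The section Cancer diagnosis in the time of COVID-19 adds a before-and-after analysis in the participating practices. For the comparison year it specifies "supplementary downloads from participating practices for the 12 months prior to March 2020 (baseline comparison period"). For the later period it specifies data "for the entire pandemic period, or until 31 October 2020, whichever is latest". Eight outcomes are listed, among them presenting symptoms, primary care interval, total time to diagnosis and number of consultations in the interval.

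Other sections bear on how much history these outcomes need:

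- Primary outcome: "we will search the patient record for coded symptoms during the year prior to diagnosis for all patients with a cancer diagnosis". Table 2 uses the same one-year horizon for total time to diagnosis and for consultations.
- Data extraction: "Data from the previous 24 months are required to identify cancers detected in 12 months prior to start", together with first symptoms up to a year before diagnosis. For the main study, "At these two time points, consultation data from the participating practices will be obtained for the previous 24 months", the two points being the start and end of the stepped wedge.
- Statistical analysis: "Extracted data from the primary care record will be limited to the study period plus the preceding year", and "Missing data for these variables in the record will be interpreted as the absence of symptoms or referral, respectively".

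On the timing of the trial itself, the COVID section says only that "the initiation of the CASNET2 study has been delayed in an attempt to minimise the effect of these factors". It gives no new start date.

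**The concern.** An interval measured backwards from diagnosis can only be as long as the record that is visible. If the baseline download starts where the baseline diagnosis year starts, a cancer diagnosed on 1 April 2019 has 31 days of history and one diagnosed at the end of February 2020 has about a year. Pandemic cancers do not have this problem, because the baseline year serves as their look-back. The truncation therefore falls on one side of the comparison only.

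The loss would also be silent, because the plan reads an absent symptom record as no symptom. A later symptom then takes the place of the true first one, or the case has no interval. Baseline intervals and consultation counts come out too low, and the mix of presenting symptoms tilts towards those recorded close to diagnosis. The result is an apparent lengthening in the pandemic, which readers would expect and might not question.

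The second issue is the end of the pandemic window. It has a minimum end date but no maximum, it uses the practices that will receive the toolkit, and no rule says what happens to records after activation.

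**Working it through.** **1. The protocol's own rule.** 12 months of diagnoses + 12 months of look-back = 24 months, as Data extraction states. Applied to a baseline year ending at March 2020, records are needed from about March 2018. The COVID section names a download starting about March 2019.

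**2. Look-back on the literal reading.** Take records from 1 March 2019 and diagnoses from 1 March 2019 to 29 February 2020 (366 dates). Look-back = min(365, diagnosis date − first extracted date).

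- Baseline: 0 to 365 days. Mean = (0 + 1 + … + 365)/366 = 182.5 days = 6.0 months. One date in 366 (0.3%) has the full year.
- Pandemic (1 March to 31 October 2020): every date has the full 12 months.
- With records from 1 March 2018: 12.0 months for every cancer in both periods.

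**3. Can the main extraction fill the gap?** It reaches 24 months before the wedge start. To reach March 2018 the wedge would have to start by March 2020, which the stated delay rules out. The extraction at the end of the wedge reaches back less far. Mean baseline look-back by assumed start:

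| Assumed wedge start | Mean baseline look-back (months) | Share with full year |
|---|---|---|
| 1 Sep 2020 | 10.5 | 50% |
| 1 Nov 2020 | 9.3 | 33% |
| 1 Jan 2021 | 7.8 | 16% |
| 1 Mar 2021 | 6.0 | 0.3% |

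**4. Illustrative size.** From the Sample size section: interval median 5 days, IQR 0–27, 90th centile 60. Assumed: linear quantiles between these points, an upper tail to 300 days, a fixed referral-to-diagnosis lag of 14, 30 or 60 days, and diagnoses uniform over the year (1,000,000 simulated cancers). A first symptom is visible only if interval + lag ≤ look-back. Affected cases are either dropped, or cut off at the start of the download (cases whose referral also precedes it being excluded). With full look-back the mean is 29.1 days, the median 5.0 and the 90th centile 60.

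| Lag (days) | First symptom lost | Mean: dropped / cut off | Median | 90th centile |
|---|---|---|---|---|
| 14 | 11.8% | 19.1 / 23.4 | 4.2 / 4.9 | 49 / 56 |
| 30 | 16.2% | 18.6 / 23.0 | 4.2 / 4.8 | 48 / 56 |
| 60 | 24.4% | 17.4 / 22.5 | 4.1 / 4.8 | 47 / 55 |

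The mean is thus short by 29.1 − 23.4 = 5.7 days at least and 29.1 − 17.4 = 11.7 days at most. If the main extraction is also used, with an assumed start of 1 November 2020, 2.1–3.3% of first symptoms are lost and the mean is 22.7–27.8 days.

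**5. Sensitivity to the tail.** A second simulation matched to the same 5, 27 and 60 days has a full-look-back mean of 19.9 days. With an assumed lag averaging 30–45 days, 14–18% of first symptoms are lost, the mean interval is about 3.3–3.5 days short and total time to diagnosis about 6–10 days short. With four extra months of history these fall to about 0.8–1.0 and 1.3–2.9 days.

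**6. Which outcomes depend on look-back.** Four of the eight do: presenting symptoms, primary care interval, total time to diagnosis, and consultations in the interval. Three do not: site and stage, direct access investigation rates, and referral rates. Emergency presentation needs no symptom history. It does need the referral to be visible, and in step 4 the referral precedes the literal download for 4%, 8% and 16% of baseline cancers at the three lags. Table 2 provides for practice queries and algorithms there, so no claim is made about that outcome.

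**The case against.** The strongest reply is that the parenthesis in the COVID section labels a comparison period and not the full extent of the records. The article uses similar shorthand elsewhere: Figure 1 and the Sample size section speak of 12 months before the intervention, while Data extraction takes 24 months to support that year. With the one-year symptom search and the general limit of study period plus preceding year, a reader could supply the missing year. This part stands: the literal reading is not certain. But the sentence describes downloads, and nothing says that the general limit covers them. The text as written therefore conflicts with the protocol's own rule.

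It also stands that the downloads are supplementary, so the main extraction may restore part of the history. It cannot restore all of it.

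A reader might go further in three ways that the documents do not support:

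- *That the pandemic window overlaps toolkit activation.* Neither the new wedge start nor the end of the pandemic period is given, and the start was delayed to limit pandemic effects. Overlap is a possibility only. Nor would it make the two effects inseparable: switch dates are scheduled and randomised, so active time can be censored or modelled.
- *That the whole COVID analysis is distorted.* At least three of the eight outcomes do not depend on look-back.
- *That the bias is a known number of days.* The size rests on assumed tails and lags, the median barely moves, and the article does not say that means will be compared.

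**Conclusion.** The concern holds in limited form. As written, the baseline download lacks the look-back year that the protocol requires elsewhere, and the resulting truncation is one-sided: mean look-back 6.0 months at baseline against 12.0 in the pandemic. This follows from the dates alone. The direction, apparent lengthening in the pandemic for the interval and consultation outcomes, follows from the definitions.

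The size is illustrative. Across the assumptions tried on the literal reading, about 12–24% of baseline first symptoms are lost and the mean primary care interval is roughly 3 to 12 days too short. The 90th centile falls from 60 to about 47–56 days, and the median from 5 to between 4 and 5. If the main extraction is used and reaches four months further back, first symptoms lost fall to about 2–3% in the first simulation, and the shortfall in the mean to between about 1 and 6 days across both. If the team already intends a preceding year, there is no bias and only the wording needs correcting.

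The open end of the pandemic window is a secondary, conditional risk. Neither issue touches the randomised primary comparison.

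**What to change.** State in the COVID section that the baseline download covers the 24 months before March 2020: 12 months of diagnoses plus 12 months of look-back. Every baseline and pandemic cancer then has a full year of visible history.

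Also give the pandemic window an upper limit: end it at the first toolkit activation, or censor each practice at its scheduled switch date.

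The cost is a wider date filter on an automated download, and so an additional year of pseudonymised records, possibly with an amendment. If the pandemic and the wedge do overlap, the cap loses some pandemic follow-up; censoring practice by practice loses less than stopping at the first activation. Both changes are cheapest before the downloads are run.
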